### Interventions

Participants will complete 16 training sessions of sequentially combined physical and cognitive training, or the corresponding control activities. Participants will be trained in small groups on 2 days per week for 2 h. The first 60 min of each session will be dedicated to the exercise intervention (EI) or the exercise control activity (EC), followed by 60 min of cognitive training with video games (CI) or the cognitive control activity (CC). Both CI and CC will be conducted on tablets (Brigmton BTPC 1018OC). EI and EC will be led by physical exercise instructors and accompanied by a music soundtrack.

#### Cognitive intervention

In each session, participants in the CI group will play 10 video games selected from the commercial Lumosity computerized training program (http://lumosity.com/). Lumosity provides a series of games targeting the improvement of several cognitive functions. Table 1 presents a short description of the games and their trained domains. These functions are sensitive to age-related cognitive decline and closely related to the ability to perform activities of daily living, such as driving. The participant will play the games in a predetermined sequence, for approximately 5–10 min for each game. Each participant in the CI group will have a Lumosity user account assigned. These games are adaptive—meaning that as performance improves, the difficulty increases, progressively adjusting to the participant’s performance level.

**Table 1 Tab1:** Short description of the video games for the cognitive intervention

Game name	Trained function	Description
Train of Thought	Divided attention	The player directs trains to their matching station
Assist Ants	Divided attention	The player prevents collisions by placing obstacles in their paths
Trouble Brewing	Divided attention	The player simultaneously serves orders to different customers
Playing Koi	Divided attention	The player keeps track of which fish has already been fed, in a square of randomly appearing fishes
Memory Serves	Working memory and divided attention	The player matches different pieces of luggage to their corresponding owners
Disillusion	Flexibility	The game consists of matching tiles with different shapes, colors, or symbols
Ebb and Flow	Flexibility	The player swipes in the direction to which the leaves are moving or pointing
Master Piece	Spatial reasoning	The player reorientates a shape so that it fills a hollow section
Speed Pack	Visualization	The player has to fit the last item into an already filled suitcase
Highway Hazards	Information processing	The player dodges obstacles in a race through a virtual desert

#### Physical intervention

The exercise intervention will consist of BODYATTACK™, which is a registered trademark of moderate to high-intensity training that combines aerobic exercises with strength and balance exercises. During the exercise protocol, participants will train at 65–80% of their maximum heart rate. The training sessions are predetermined by the distributer and comprise standardized movements, exercises, and music soundtracks (see Table 2). Exercises include large plyometric movements and more controlled movements, and train equally upper and lower body muscles with dynamic movement coordination. The sequence of exercises is as follows: 10-min warm-up, 35-min main phase (with active recovery between intervals), and 10-min cool-down.

**Table 2 Tab2:** Description of the exercise intervention

Activity	Trained function	Description
Adaptation of “BODYATTACK™”	Cardiovascular fitness	Aerobic exercises
	Endurance	Strength moves
	Coordination	Movements to music soundtrack
	Balance	Stabilization exercises
	Flexibility	Stretching

#### Cognitive control activity

The cognitive control component will exclusively involve language-specific processes and crystalized knowledge (see Table 3). These domains are preserved with age, and even though an implication of executive functioning cannot be ruled out, this is clearly not the main active component. The cognitive control games are available within the gaming service Google Play Games, which mimics cognitive training platforms. This will create the impression of receiving an intervention, thereby reducing expectation biases. Participants will play 10–15 min each game in a predetermined sequence.

**Table 3 Tab3:** Short description of the video games for the cognitive control condition

Game name	Trained function	Description
Hangman	Lexical access	The player guesses a word by suggesting letters within a certain number of guesses
Grammar	Lexical access	The player chooses the correct spelling of a word within three possibilities
Definitions	Semantics and lexical access	The player chooses the correct word according to a given definition
Word search	Lexical access	The player identifies words hidden in a grid filled with letters
Crossword	Semantics and lexical access	The player constructs words by solving clues
Synonyms and antonyms	Semantics and lexical access	The player produces a word with a similar or opposite meaning of a given word
Trivia quiz	Crystalized knowledge	The player answers to questions of general knowledge

#### Physical control activity

The physical control activity will consist of BODYBALANCE™ (https://www.lesmills.com/), which is a music-guided exercise that combines Tai Chi, Yoga, and Pilates exercises. The sequence of exercises of each session is as follows: 10-min warm-up with Tai Chi exercises; 35-min main phase with Yoga and Pilates exercises with a focus on breathing, stretching, balance, and strengthening of abdominal muscles; and 10-min cool-down with meditation and relaxation. The physical activity intervention and the physical control activity are briefly described in Table 4.

**Table 4 Tab4:** Description of the activities of the exercise control condition

Game name	Trained function	Description
Adaption of “BODYBALANCE™”	Flexibility	Stretching
	Relaxation	Respiratory exercises

### General procedure

After baseline, participants who meet the inclusion criteria will be randomly assigned to one of the four groups. The active control group was introduced in the design to control for placebo effects [84]. The main question is whether the multidomain group will outperform the single-domain groups at posttest, and whether these groups will outperform the active control group in a series of cognitive-control and memory tasks (see below). We focused on these cognitive domains because they deteriorate with age and are critical for independent living.

All methodological designs of primary and secondary outcomes are constructed using the rules of counterbalance and stimulus rotation. Response keys will be counterbalanced across conditions. The computerized tasks have been programmed with E-Prime 2.0 (Psychological Software Tools Inc.). Continuous EEG activity will be recorded in our laboratories with thin electrodes from 40 scalp sites using NuAmps amplifiers while participants perform the task-switching task.

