### Objectives and hypotheses

The main objective of this randomized controlled trial (RCT) is to investigate the synergetic effects of a group-based multidomain training program that combines cognitive video-game training with physical exercise, in comparison to those produced by cognitive training combined with physical control activity, physical training combined with cognitive control activity, or a combination of both control activities, on behavioral and electrophysiological measures of executive control (set-shifting, response inhibition, and information updating and monitoring) and memory functions (immediate and delayed visual and verbal memory). These cognitive functions, which are often compromised in later years, are essential for everyday activities. The second objective is to investigate whether event-related potential (ERP) latencies of the P2 component are shorter and N2 and P3b components assessed in a memory-based task-switching task are enhanced after training. Electrophysiology provides a very useful online measure to identify the contribution of different processing stages of executive functioning. ERPs can help us to understand the specific executive control impairments occurring with age, as well as the possible effects of the different types of intervention investigated in this RCT. To this end, the task-switching paradigm is a valid task that helps to identify the cognitive processes that most decline with ageing [75]. However, electrophysiological studies conducted to evaluate training-related effects in older adults using this task are scarce [76]. Finally, we are interested in finding out whether possible enhancements persist after a 3-month period without training.

We expect to find greater behavioral improvements in executive control and memory functions after training, larger maintenance effects, and shorter ERP latencies of the P2 component and enhanced N2 and P3b components in the multidomain training condition in comparison to both single-domain conditions. We also expect the multidomain group and both single-domain groups to outperform the active control group at the 3-month follow-up period.

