### Study design

Participants will complete one of the four combinations of cognitive training with video games and physical exercise. The cognitive component will be either a brain-training video-game program selected from Lumosity (cognitive intervention, CI) or video games not specifically designed to train particular cognitive functions such as attention, memory, or executive control (cognitive control, CC). The physical exercise component will be either a senior-friendly adaption of BODYATTACK™ (https://www.lesmills.com/), a combination of dance, aerobic, strength, and muscular resistance (exercise intervention, EI), or its control condition comprising stretching, toning, and relaxation (exercise control, EC). The duration of sessions for all groups will be the same, and all participants will perform physical exercise and video-gaming activities in a social environment (in small groups formed by 10–12 participants) and in the presence of the trainer.

To summarize, the study will have a 4 × 3 mixed factorial design with four intervention conditions—multidomain (CI + EI), uni-domain cognitive intervention (CI + EC), uni-domain physical intervention (EI + CC), and active control (CC + EC)—assessed at three different time points (pretest, posttest, 3-month follow-up), with “Type of training” as between-subject factors and “Time” as the within-subject factor. The dependent variables will be behavioral and/or electrophysiological measures of executive functions (inhibition, shifting, working memory), memory functions (short term and long-term visual and word memory), and emotional well-being, quality of life, and motivation.

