### Sample size

We conducted an a priori power analysis using G*Power 3.1 [80] to calculate the appropriate sample size. Using an α value of 0.05, power of 0.80, and a medium effect size (*f* = 0.38) for video-game training [45] and physical training [81], and four groups within the *F*-test family, a total sample size of 124 is required. Considering a dropout rate of 12%, a total of 144 participants would be sufficient to detect significant main effects. According to this calculation, the adequate number of participants in each group (multidomain training, video-game training, physical activity training, and active control) is 36. According to this, we will set a sample size of 36 participants per arm, which is adequate for the experimental design. According to Montgomery et al. [82], with this number of participants the design would be underpowered to detect an interaction effect, as it would need a fourfold increase in sample size. However, given that lower interaction effects would not be clinically relevant, we decided to maintain our initial sample size estimation.

In the elaboration of this protocol, we have followed the SPIRIT 2013 explanation and elaboration guidance for reporting protocols of clinical trials [83].

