### Statistical analysis

All data from participants with complete baseline assessment and who attended at least one training session will enter into a primary intention-to-treat analysis. For the secondary per-protocol analysis, only the data of participants with a complete cognitive assessment and an attendance rate ≥ 70% will be considered.

Executive functions (set shifting, maintenance, inhibitory control) and memory functions (short-term, visual, and verbal immediate and delayed memory) will be assessed at pretest, posttest, and follow-up. The statistical analysis corresponding to the behavioral results will be carried out with the SPSS statistical package for Windows (SPSS 25.0; IBM Corporation). Results will be considered significant at *p* < 0.05, with Bonferroni-corrected post hoc tests performed as appropriate. We will explore the missing data to ascertain their pattern and will apply an adequate technique of multiple imputation. Repeated ANOVA measures will be conducted with four groups (multidomain training, cognitive training, exercise training, active control) at three time points (pretest, posttest, follow-up) to test the primary hypothesis (i.e., differences in efficacy between interventions compared to the active control condition). Repeated ANOVA measures will also be performed to determine the effect of the interventions on secondary outcomes. To evaluate the effect size of the combined multimodal group versus each individual intervention group and the control arm, we will use multimodal regression with an interaction term. Electrophysiological data will be analyzed with CURRY 8.0.2, the EEGLAB toolbox [92], and the ERPLAB plugin for EEGLAB [98].

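### The main objective is synergy, but the main question would also be answered yes if two benefits merely add, and nothing ties a synergy conclusion to the interaction contrast

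*Protocol article*

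**What the plan says.** Objectives and hypotheses opens with the aim: "The main objective of this randomized controlled trial (RCT) is to investigate the synergetic effects of a group-based multidomain training program". The Abstract uses the same term. The expected result is then put as a pairwise comparison. Behavioural gains should be larger with multidomain training than with either single-domain programme, and the electrophysiological prediction is worded alike: "enhanced N2 and P3b components in the multidomain training condition in comparison to both single-domain conditions".

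General procedure names the question to be answered: "The main question is whether the multidomain group will outperform the single-domain groups at posttest". The same sentence goes on to ask whether these groups do better than active control.

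Study design crosses two versions of the cognitive component (CI, CC) with two of the exercise component (EI, EC), but treats the result as one four-level factor: "the study will have a 4 × 3 mixed factorial design with four intervention conditions". In Statistical analysis the repeated-measures ANOVA is meant "to test the primary hypothesis (i.e., differences in efficacy between interventions compared to the active control condition", followed by Bonferroni-corrected post hoc tests. An interaction term appears once, in a regression whose purpose is "To evaluate the effect size of the combined multimodal group versus each individual intervention group and the control arm".

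Sample size concedes that the design is underpowered for an interaction and keeps the sample size on the ground that smaller interactions would not matter clinically.

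**The concern.** Superiority over each single-domain arm and synergy are different claims. CI+EI minus CI+EC is the effect of adding active exercise to cognitive training. CI+EI minus EI+CC is the effect of adding cognitive training to active exercise. The null hypothesis in each is that the second component adds nothing. Two useful components that work independently make both differences positive with no synergy at all. The further comparison of the single-domain groups with active control does not help, because additive effects satisfy that too.

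At stake is the answer to the stated first objective. A yes to the main question could be reported under a heading of synergy when the data show only that two active components do more than one. Greater power in the pairwise comparisons would make that misreading more frequent.

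**Working it through.** **Inputs.** From Sample size: f = 0.38, two-sided significance level 0.05 for the F test, 124 participants before dropout (31 per arm), 144 after (36 per arm). From Statistical analysis: Bonferroni post hoc tests, with the number of comparisons not given, so none, two and six are shown. Assumed: unit SD on the analysed change score, independent arms, two-sided pairwise tests, pooled four-arm variance.

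**The plan's own figure.** The section gives "Using an α value of 0.05, power of 0.80", f = 0.38 and four groups. A one-way ANOVA with noncentrality N·f² then needs N = 80. The stated 124 corresponds to power 0.95 (computed 0.952). That is a separate matter; both 31 and 36 per arm are used here. The dropout step is consistent: 124/0.88 = 140.9, and 144 = 4 × 36.

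**The contrasts**, with control mean 0, component effects a and b, and interaction I:

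- CC+EC = 0, CI+EC = a, EI+CC = b, CI+EI = a + b + I
- (CI+EI) − (CI+EC) = b + I
- (CI+EI) − (EI+CC) = a + I
- (CI+EI) − (CI+EC) − (EI+CC) + (CC+EC) = I

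Only the last isolates synergy. With I = 0, the first two differences are b and a.

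**Effect size.** For additive means 0, d, d, 2d, the SD of the four means is √(2d²/4) = d/√2. So f = 0.38 gives d = 0.38 × 1.414 = 0.54.

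**Chance that multidomain significantly beats both single-domain arms when I = 0** (200,000 simulated trials per row group, one outcome; 31 per arm / 36 per arm):

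| Effect of each component | Uncorrected | Bonferroni, 2 | Bonferroni, 6 |
|---|---|---|---|
| 0 | 0.5% / 0.5% | 0.2% / 0.2% | 0.0% / 0.0% |
| 0.2 SD | 4.1% / 4.9% | 2.0% / 2.5% | 0.6% / 0.8% |
| 0.3 SD | 9.8% / 11.7% | 5.4% / 6.6% | 2.0% / 2.6% |
| 0.4 SD | 19.5% / 23.3% | 12.0% / 14.8% | 5.3% / 6.9% |
| 0.54 SD | 39.2% / 46.2% | 27.9% / 34.2% | 15.1% / 19.8% |
| 0.76 SD | 74.9% / 82.2% | 64.0% / 73.0% | 46.4% / 56.7% |

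The last row applies only if f = 0.38 is read as a two-group effect, d = 2f = 0.76. With one active component (0.76 and 0 SD, 36 per arm) the rates are 2.5%, 1.2% and 0.4%.

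In every additive setting the interaction contrast is significant in about 5% of trials two-sided and 2.5% in the favourable direction.

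**Precision of the interaction contrast.** Its standard error is √(4/n), against √(2/n) for a pairwise difference, a ratio of √2 = 1.41. At 36 per arm it is 0.333 SD, so the 95% CI is about ±1.98 × 0.333 = ±0.66 SD. Power at 31 / 36 per arm is 32% / 36% for a true interaction of 0.54 SD and 79% / 85% for 1.0 SD. The fourfold sample-size penalty in Sample size fits this contrast: its variance is 16/N, against 4/N for a factorial main effect.

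**The case against.** The strongest reply is that the protocol contains no rule declaring synergy when both single-domain arms are beaten. General procedure does not use the word. It asks whether the combination outperforms its components, which is a legitimate question. The objective itself is phrased as a comparison with the other arms, and the Abstract's background and discussion describe the same aim without the word. On that reading the defect is one loosely used adjective. This stands in part: the link between objective and question is read from two sections, not stated in one. But the term heads the main objective and the Abstract's objectives, so it would naturally frame the reported conclusion.

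Second, an interaction term is planned. A reader might infer that the interaction has been overlooked; the documents do not support that. The regression may well contain the right contrast, and Sample size shows that its low power was recognised. The coding is not given, however, and the stated purpose is effect size against the other arms. Coding can be left to a fuller plan. The mismatch between the stated objective and the stated main question cannot.

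Third, the rates are conditional. A reader might quote the uncorrected 39–46% as the trial's false-positive rate for synergy. That ignores the Bonferroni correction that Statistical analysis specifies and the need for both components to have real, additive effects. Rates for beating at least one single-domain arm are not relevant either, because the main question concerns the single-domain groups together. These limits stand.

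**Conclusion.** The concern holds as a mismatch between the main objective and the question set to answer it. Under purely additive benefits of 0.54 SD each, the main question is answered yes on one outcome in 15–20% of trials with Bonferroni over six comparisons, 28–34% over two and 39–46% uncorrected. The corresponding figure for the interaction contrast in the favourable direction is 2.5%.

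The excess requires both components to work. It is gone at 0.3 SD with six-way Bonferroni, and absent when neither component or only one has an effect. Benefit from both is, however, what the protocol expects and what it sizes the trial on.

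It would go too far to say that the protocol will declare synergy wrongly at these rates, since no section sets such a rule. What can be said is that following the main question as written can give a wrong answer to the first objective, and that nothing in the protocol prevents it. The data and the group comparisons themselves are unaffected.

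**What to change.** In Objectives and hypotheses, General procedure and Statistical analysis, separate two claims:

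1. **Added benefit:** multidomain minus each single-domain arm, on change from baseline at posttest.
2. **Synergy:** the CI × EI interaction contrast, (CI+EI) − (CI+EC) − (EI+CC) + (CC+EC), on the same measure and time point, reported with its 95% CI. Make this the only basis for a synergy claim, and make the claim only if the interval excludes zero in the favourable direction.

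State that superiority over both single-domain arms alone will be reported as added benefit, and repeat beside the contrast the imprecision that Sample size already concedes.

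Alternatively, drop the word synergetic, in the Abstract as well, and restate the objective as superiority of the combination over each component.

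The cost is wording plus, for the first option, one contrast from the same four arms, with no new data or participants. The downside is that a synergy claim becomes harder to make, because the contrast's standard error is 1.41 times that of a pairwise difference.

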### Outcome measures

Each group will be assessed at three time points. Possible improvement will be assessed at posttest (12 weeks) and follow-up (24 weeks) using baseline (week 0) outcomes as a reference point. A schematic diagram of the time schedule of data collection for all outcome measures is shown in Fig. 2 (see also Additional file 1: SPIRIT checklist).

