### Participants

Participants will be male and female, healthy, and independently living volunteers aged between 60 and 80 years. Those who complete the baseline assessments and meet the inclusion criteria (see later) will be randomly assigned to one of the four intervention conditions. The timing of group allocation will take place between 1 and 8 weeks after baseline.

Participants may discontinue their intervention for personal or medical reasons. To minimize dropouts and improve adherence to the intervention, four face-to-face adherence reminder sessions will take place during the training program emphasizing the importance of training compliance. Furthermore, to increase participant retention and to reduce loss to follow-up, all participants will receive a personalized report of their performance and training progress at the end of the study. Participants will receive a small refund in compensation for their travelling expenses.

Even though this trial is low risk, participants might harm themselves during the practice of physical exercise. To minimize the risk of injuries, each participant will be carefully monitored during the training sessions. The interventions will be designed in collaboration with the exercise instructors, after a detailed analysis and taking into account each participant’s possible medical issues. Spontaneously reported adverse events or other unintended effects will be registered and analyzed, and if necessary the protocol will be modified to eliminate the causing element. We have signed an insurance policy in case any participant suffers harm during the physical training.

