### Randomization and blinding

After the baseline assessments, participants will be randomly allocated to one of the four training protocols in a stratified process using the online tool Random Lists (move this to the other linehttps://www.randomlists.com/). [name] will generate the random sequence and will assign participants to interventions. At first, participants who came in couples will be randomly allocated as a unit to one of the four groups, and afterward the same procedure will be performed with the individual participants. This procedure aims to minimize dropouts due to separating couples in different groups. Participants and exercise instructors will be blinded to treatment allocation (single-blind). Data analysis will not be blinded, as it will be performed by the investigators who actively collaborate in the study. We do not envision any reason why participants should be unblinded, either during the trial or at the end of the study.

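### Posttest and follow-up fixed at weeks 12 and 24 from baseline do not fit allocation up to 8 weeks after baseline followed by 8 weeks of training

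*Protocol article*

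**What the plan says.** All of the relevant statements are in the protocol article.

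- **Outcome measures** gives the assessment times and their origin: "Possible improvement will be assessed at posttest (12 weeks) and follow-up (24 weeks) using baseline (week 0) outcomes as a reference point". The text shown gives no visit window.
- **Participants** gives the delay before allocation: "The timing of group allocation will take place between 1 and 8 weeks after baseline". **Randomization and blinding** confirms the order: "After the baseline assessments, participants will be randomly allocated to one of the four training protocols".
- **Interventions** gives the amount and pace of training: "Participants will complete 16 training sessions of sequentially combined physical and cognitive training, or the corresponding control activities", and "Participants will be trained in small groups on 2 days per week for 2 h".
- **Objectives and hypotheses** states what the follow-up is for: "we are interested in finding out whether possible enhancements persist after a 3-month period without training". The Objectives paragraph of the abstract says the same.

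The schedule diagram (Fig. 2) and the flow chart (Fig. 1) are not available in the text reviewed.

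**The concern.** The two assessments are counted from baseline, but training starts after a delay that may differ by up to 7 weeks between participants. A fixed week 12 then has no fixed relation to the end of training, and a fixed week 24 has no fixed relation to the start of the training-free period.

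This matters for two comparisons. The General procedure section makes posttest the occasion of the main question, and the behavioural primary outcomes are changes from baseline to posttest and follow-up. If the weeks were followed as written, one posttest label would cover people partway through the programme and people some weeks past it. Partial exposure pulls the estimated training effect down and adds variance. The persistence objective needs a defined interval without training, and the stated weeks do not deliver one.

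**Working it through.** **Inputs.** Posttest at week 12 and follow-up at week 24, with baseline as week 0 (Outcome measures). Allocation at week *a*, where *a* runs from 1 to 8 (Participants). 16 sessions, 2 per week (Interventions). Intended training-free interval of 3 months, about 12 to 13 weeks (Objectives and hypotheses).

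**Assumption.** Training starts at allocation and no session is missed. This is the most favourable case for the protocol; any delay between allocation and the first session moves the end of training later.

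**Formulas.**

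- Length of training = 16 / 2 = 8 weeks (derived; the article does not state it as a duration).
- End of training = *a* + 8.
- Sessions possible by week 12 = the smaller of 16 and 2 × (12 − *a*).
- Training-free weeks at week 24 = 24 − (*a* + 8) = 16 − *a*.

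| Allocation week | End of training (week) | Sessions possible by week 12 | Training-free weeks at week 24 |
|---|---|---|---|
| 1 | 9 | 16 | 15 |
| 2 | 10 | 16 | 14 |
| 3 | 11 | 16 | 13 |
| 4 | 12 | 16 | 12 |
| 5 | 13 | 14 | 11 |
| 6 | 14 | 12 | 10 |
| 7 | 15 | 10 | 9 |
| 8 | 16 | 8 | 8 |

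**When the plan's own figures are reproduced.** Posttest to follow-up is 24 − 12 = 12 weeks. That equals the training-free interval only if training ends at week 12, so 12 − 8 = 4 weeks from baseline to the first session. With *a* = 4 every stated figure fits. With *a* from 1 to 3, training is finished 3 to 1 weeks before posttest. With *a* from 5 to 8, week 12 falls 1 to 4 weeks before training can end.

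**Does another origin rescue the weeks?** Suppose week 0 meant allocation or the start of training. Training would end at week 8, posttest would come 12 − 8 = 4 weeks later, and follow-up would come 24 − 8 = 16 weeks after the last session. Nobody would be tested during training, but the interval would exceed three months and the explicit baseline origin would be contradicted.

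**Link to the per-protocol rule.** Statistical analysis sets an attendance threshold of 70%. By week 12 a participant allocated at week 7 could have attended at most 10/16 = 62.5% of sessions, and one allocated at week 8 at most 8/16 = 50%.

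**The case against.** The best reply is that weeks 12 and 24 are nominal labels for a typical participant. The midpoint of the allocation range is (1 + 8) / 2 = 4.5 weeks, close to the 4 weeks at which everything fits. The visit is called a posttest throughout, the hypotheses speak of improvement after training, and the follow-up is defined by a period without training. Staff could reasonably test after the last session whatever the calendar says. Fig. 2 might also show a different anchor, and an article may leave visit windows to a fuller protocol.

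Much of this stands. A reader might infer that the trial plans to test some participants in the middle of training. The document does not support that: it follows only if the week number is put above the meaning of posttest. A reader might also infer that the three timing statements can never hold together. They can, for allocation by week 4. Nor is there support for bias between arms: allocation is random, the four groups are trained in three waves (Trial setting), and nothing shown suggests that the delay differs by arm.

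What does not stand is the suggestion that the point is merely condensed detail. The article itself states the delay, the number and pace of sessions, the assessment weeks and their origin, and for part of the permitted range these conflict. Nothing in the text shown calls the weeks approximate or ties them to the end of training.

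**Conclusion.** The inconsistency is real and of moderate severity; it is not one that must be resolved before the trial can be interpreted at all. As written, the assessment weeks cannot hold for participants allocated after week 4. Across the permitted range, training ends at weeks 9 to 16 at the earliest, and the training-free interval at week 24 is 15 down to 8 weeks instead of about 12 to 13.

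The size of the effect on the results is unknown. Neither the distribution of allocation times nor the wave dates are given, so the number of participants affected and the dilution cannot be computed. Under literal scheduling the likely consequences are a diluted posttest effect, extra variance and a persistence result that mixes different intervals. Under nominal scheduling the mid-training problem disappears, but the article must say that this is what is meant. No sample size, power or alpha figure depends on this point.

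**What to change.** Reconcile the Participants, Interventions and Outcome measures sections:

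- Define posttest relative to each training group's last scheduled session, with a stated window.
- Define follow-up as three months after that same date, so that the training-free interval is the one named in the objectives.
- Describe weeks 12 and 24 as nominal, or correct them. With posttest directly after training and follow-up 12 weeks later, the visits fall at about weeks 9 to 16 and 21 to 28 from baseline.
- Record for each participant the lag from baseline to first session and the days since the last session at each assessment, so that the spread, and its balance across arms, can be reported.

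The cost is wording and a scheduling rule. Training already runs in groups and waves, and the number and pace of sessions stay as they are. The small downside is that time from baseline to posttest will then vary between participants, by up to 16 − 9 = 7 weeks under the assumption above; the recorded lag makes that visible.
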